#### 2.3.4 Recovery modalities

##### 2.3.4.1 Diaphragmatic breathing exercises

Subjects will be in crook lying position. They will be advised to deeply inhale through the nose so that they could see their abdomen expanding. They should hold this position for 5 s and then exhale through mouth. To ensure that the subjects are performing the exercise correctly, they will be instructed to place one hand on their chest and the other on their abdomen. They will be advised to breathe in so deeply that they should feel only the movement of the hand on their abdomen and not that of the hand on their chest. Each subject will perform the assigned exercise 10 times per session. They will take 1-min rest between each session (Rasheed et al., 2021).

##### 2.3.4.2 Passive recovery

The subjects will be asked to lie on a bed in a darkened room and do nothing for 24 min after Abt’s trunk muscle fatigue protocol (Seidi et al., 2019).

### 2.4 Statistical analysis

Statistical analyses will be carried out using SPSS Statistics (SPSS Statistics Version 24; IBM Corporation^©^, United States). Prior to statistical comparisons, a Shapiro-Wilk test of normality will be performed for all variables. Not normally distributed data will be analyzed using nonparametric tests. Friedman’s test followed by Dunn’s *post hoc* test will be used for the comparison of the spinal mobility, postural stability and EMG variables at different assessment times (at baseline, immediately after Abt’s fatigue protocol, immediately after recovery modalities, 15-min after recovery modalities, 30-min after recovery modalities). The Kruskal–Walli’s test will be used for the inter-group comparisons (experimental group A vs. experimental group B) at each assessment. For the normally distributed data, a repeated measures Analysis of Variance (ANOVA) will be performed. Repeated measures ANOVA will be used to confirm if there are differences in each group (within-group comparisons), considering each group in isolation, between the five assessments in each of the spinal mobility variables (at baseline, immediately after Abt’s fatigue protocol, immediately after recovery modalities, 15-min after recovery modalities, 30-min after recovery modalities). To calculate between-group differences from baseline assessment to final follow up, a five-way repeated-measures ANOVA will be performed. With the spinal mobility and/or postural stability and/or EMG variables outcome as dependent factor, with five levels corresponding to every time of assessment (t1, t2, t3, t4, and t5), and the two groups (experimental group A vs. experimental group B) as independent factors. The Bonferroni correction will be applied to control for the increased probability of significant findings due to multiple testing. Between- and within-group effect sizes for all quantitative variables will be measured with the Cohen d coefficient: small effect (less than d = 0.2 and ηp2 = 0.01); moderate effect (approximately d = 0.5 and ηp2 = 0.06); and large effect (greater than d = 0.8 and ηp2 = 0.14) (Cohen, 2013). The α-level will be set to 0.05 for all statistical tests.

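### A normality pretest chooses the analysis outcome by outcome, and the rank branch has no modality-by-time test and ignores that the same participants receive both modalities

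*Protocol article*

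**What the plan says.** All of the rule is in section 2.4 (Statistical analysis) of the protocol article.

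- Pretest: "Prior to statistical comparisons, a Shapiro-Wilk test of normality will be performed for all variables".
- Switch: "Not normally distributed data will be analyzed using nonparametric tests", and "For the normally distributed data, a repeated measures Analysis of Variance (ANOVA) will be performed".
- Parametric branch, between modalities: "To calculate between-group differences from baseline assessment to final follow up, a five-way repeated-measures ANOVA will be performed". Despite the label, the factors described are time with five levels and group with two.
- Rank branch, over time: Friedman's test followed by Dunn's test across the assessment times.
- Rank branch, between modalities: Kruskal-Wallis, which "will be used for the inter-group comparisons (experimental group A vs. experimental group B) at each assessment".

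Three other places bear on this. The Abstract says the same twenty adults undergo active and then passive recovery, one week apart, and hypothesises that active recovery restores function better. Section 2.2.2 sizes the trial for a within-between interaction in a repeated-measures design. Section 2.3.2 lists four assessments (baseline, post-fatigue, immediately after recovery and 15 minutes later), whereas section 2.4 lists five, adding one at 30 minutes.

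**The concern.** The switch would be a minor matter if both branches asked the same question. They do not. Only the parametric branch puts modality and time in one analysis. A normality p-value therefore decides whether an outcome receives the comparison the study was sized for.

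The trial has many related outcomes: flexion, extension and total spinal range; centre-of-pressure variables in four stance conditions; and three EMG features for several muscles. Closely related outcomes could be reported under different hypotheses for no scientific reason.

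The between-modality test in the rank branch is also a test for independent groups, applied to people who serve as their own controls. Any outcome sent there loses the main advantage of the design.

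**Working it through.** **1. The plan's own figure.** The document gives no figure for how many outcomes the pretest diverts. The nearest stated figure is the sample size of 11 in section 2.2.2, which shows the kind of test intended. The usual formula for that test uses noncentrality λ = f²·N·m/(1−ρ), with df1 = (k−1)(m−1) and df2 = (N−k)(m−1). The number of groups k, the number of measurements m and the correlation ρ are not stated, so 11 cannot be confirmed. With k = 2:

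- m = 5, ρ = 0.75: λ = 0.0625·11·5/0.25 = 13.75, df 4 and 36, power 0.805. This gives N = 11.
- m = 4, ρ = 0.8: also gives N = 11.
- ρ = 0.5: gives 24 (m = 4) or 21 (m = 5).

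The point below does not depend on which applies.

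**2. The two branches side by side.**

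| Question | Judged normal | Judged non-normal |
|---|---|---|
| Change over time within a modality | Repeated-measures ANOVA | Friedman, Dunn |
| Modalities at a given time | Within the group-by-time ANOVA | Kruskal-Wallis at each assessment |
| Does change differ between modalities? | Group-by-time ANOVA | None |

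The empty cell is the question in the Abstract's hypothesis and in the sample-size test. This holds whatever share of outcomes is diverted.

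**3. Cost of ignoring pairing.** Inputs: n = 20 (section 2.2.2), the same people under both modalities (Abstract), a difference of 0.5 SD at one time (assumed), correlation ρ (assumed), nominal 5%. A test for independent groups uses a standard error of √(2/20) = 0.316 SD, but the true one is 0.316·√(1−ρ). At ρ = 0.7, a large-sample approximation gives:

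- Size: the true threshold is 1.96/√0.3 = 3.58 standard errors, a two-sided error of about 0.03%.
- Power: (1.96 − 0.5/0.316)/√0.3 = 0.69, an upper-tail probability of about 24%.

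Simulation on normal data, 4,000 runs per setting:

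| ρ | Kruskal-Wallis size | Kruskal-Wallis power | Signed-rank size | Signed-rank power |
|---|---|---|---|---|
| 0.5 | 1.0% | 27% | 4.6% | 55% |
| 0.7 | 0.05% | 24% | 4.5% | 77% |
| 0.8 | 0.03% | 21% | 4.8% | 90% |

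Repeat runs moved these powers by about a point, so the ranges are 21–28% and 55–91%.

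**4. Share of truly normal outcomes diverted.** Each Shapiro-Wilk test is at α = 0.05. If q cells are tested and any one rejection diverts the outcome, independence gives 1 − 0.95^q: 5% for q = 1, 22.6% for q = 5, 33.7% for q = 8 and 40.1% for q = 10. Five cells means one modality only. Eight and ten mean two modalities at the four assessments of section 2.3.2 or the five of section 2.4. With correlated cells (n = 20, 4,000 runs):

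| Cells tested | ρ = 0.5 | ρ = 0.7 | ρ = 0.8 |
|---|---|---|---|
| 1 | 5.8% | 5.2% | 4.6% |
| 5 | 22.6% | 21.3% | 18.8% |
| 8 | 33.1% | 31.2% | 27.7% |
| 10 | 39.1% | 34.3% | 30.7% |

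The simulation standard error is at most about 0.8 points (√(0.391·0.609/4,000) = 0.0077). Taking independence and repeat runs together, the ranges are about 18–23%, 28–34% and 31–40% for five, eight and ten cells.

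**The case against.** A normality check with a rank fallback is conventional, and this is a condensed article. Details such as whether values or residuals are tested may sit in a document that is not shown. That is fair: the text says only that all variables are tested, so a reader who takes it to mean raw values is inferring it. The switch itself, and the tests in each branch, are stated outright.

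A reader might go further in three ways that the documents do not support.

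- **That about a third of normal outcomes would be diverted.** This needs separate testing of eight to ten cells, diversion on any one rejection, and no adjustment of the pretests. None of these is stated, and one test per variable gives 5%.
- **That a diverted outcome gets no test of the hypothesis.** Kruskal-Wallis after recovery does compare the modalities and bears on the hypothesis. What is missing is a test of the difference in change.
- **That the two-stage procedure breaks the 5% error rate.** Simulating the rule with ten cells and any rejection diverting gave 3.3–4.4% false positives when the rank branch used one Kruskal-Wallis test, and 3.8–5.2% when any of five counted. There is no material inflation.

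Nor does the power gap in the working measure the harm of pretesting. At correlation 0.7, an independent-samples t-test has 26% power against 24% for Kruskal-Wallis, so moving to ranks costs about 2 points. The rest comes from not pairing. This objection stands. It changes the cause of the loss, but not the fact that the named rank test suffers it.

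**Conclusion.** The point holds in a limited form. Section 2.4 makes the hypothesis tested depend on a pretest result, and its rank branch has neither a modality-by-time test nor a paired comparison of modalities. The first part follows from the text alone and needs no assumed figures.

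The size of the loss rests on an assumed correlation of 0.5 to 0.8 and a 0.5 SD difference at a single time: about 21–28% power for Kruskal-Wallis against 55–91% for a paired signed-rank test, with true size near zero instead of 5%. It also rests on the Abstract's account that the same participants receive both modalities. If groups A and B were different people, the pairing loss would fall away and the missing modality-by-time test would remain.

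The diversion rate cannot be fixed from the document. It should be given as 5% to about 40%, with the rule for applying the test stated alongside. The error is one of lost power and inconsistent questions, not of excess false positives. It should be corrected before analysis.

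**What to change.** Do not let the normality test choose the analysis. For every outcome, prespecify one model with participant as random effect and with modality, time and modality-by-time as fixed effects. Check its residuals without switching the test on the result.

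Replace Kruskal-Wallis with a paired signed-rank or permutation test of the within-person difference between modalities in recovery change, reported for all outcomes as a sensitivity analysis. Reconcile the number of assessments in sections 2.3.2 and 2.4, so that the time factor has a fixed number of levels.

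The change is to analysis wording only. The cost is slightly more analysis work; SPSS, the software already named, fits such a model.

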#### 2.2.2 Sample size estimation and sampling method

A prior sample size estimation was done using the G*Power software package (version 3.1.9.7) based on the study by Fonta et al. (2021). The input parameters were as follows: statistical test = repeated measures, within - between interaction; effect size F = 0.25; α err prob = 0.05; and power (1 − β err prob) = 0.80. As a result, the total sample size was calculated to be 11 subjects. In consideration of the possibility of dropouts, a slightly larger number of subjects will be recruited to participate in this study. The total sample size would be approximately 20 subjects.

A purposeful sampling strategy will be used and participants based on their age, sedentary behavior, and other relevant factors that are related to the study’s focus and have been explained in inclusion and exclusion criteria section will be selected.

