#### 2.3.2 Data collection

Data from all participants will be collected under three conditions:1. Pre-fatigue assessment (at baseline),2. Post-fatigue assessment (immediately after fatigue protocol),3. Post-recovery modalities assessment (immediately, and 15-min after cessation of active and passive modality, respectively).

Assessing the effects of the intervention at the 15-min follow-up can provide insight into the potential duration of these effects.

All participants will be tested at the same time of day by the same examiners.

The study will involve gathering individual demographic information and outcome data. The study team will enter the questionnaire data into a database and verify its accuracy before using it. All information and outcome data will be kept on password-protected computers that only the authorized members of the study team will be able to access. Data management will outline the procedures for gathering, recording, storing, and archiving data.

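### For non-normal variables, Dunn's test after Friedman is insensitive to the immediate recovery step at about 20 participants when recovery is stepwise; planned paired contrasts would be more powerful

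*Protocol article*

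**What the plan says.** All analysis text is in section 2.4. Each variable is checked with Shapiro-Wilk, and "Not normally distributed data will be analyzed using nonparametric tests". For change over time in that branch the plan states: "Friedman’s test followed by Dunn’s *post hoc* test will be used for the comparison of the spinal mobility, postural stability and EMG variables". It names no other test of time for these variables. Kruskal-Wallis is assigned to the comparison between modalities.

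On error control, the section states "The Bonferroni correction will be applied to control for the increased probability of significant findings due to multiple testing" and "The α-level will be set to 0.05 for all statistical tests". It does not say which comparisons form the family.

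Section 2.2.2 sets the size: "The total sample size would be approximately 20 subjects". The abstract has every participant go through both modalities, so each within-modality Friedman test has about 20 complete rows.

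The number of assessments is not consistent. Section 2.4 works "with five levels corresponding to every time of assessment (t1, t2, t3, t4, and t5"), the last at 30 minutes after recovery. Section 2.3.2 lists baseline, post-fatigue and then "Post-recovery modalities assessment (immediately, and 15-min after cessation of active and passive modality, respectively"), which makes four. Both counts are used below.

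**The concern.** The study is about acute recovery, and an assessment is scheduled immediately after each modality. Within a modality, post-fatigue against immediately after recovery is therefore the most direct reading of acute change.

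Dunn's test after Friedman ranks each person's assessments together and compares two mean ranks. Its standard error depends only on the number of assessments and participants. Whether two assessments differ therefore depends on how many of the other assessments rank between them, and not on how far each person moved. If recovery is gradual, post-fatigue and immediate post-recovery tend to take neighbouring ranks, and the gap stays near 1 however large or consistent the improvement is.

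At stake is the reporting of individual outcomes. A variable sent to the non-normal branch could be reported as showing no significant immediate recovery when every participant recovered, while a paired test on the same data would be clear.

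**Working it through.** **The plan's own figure.** The plan gives no figure for the sensitivity of the post hoc test. Its only sample-size figure is 11, from "effect size F = 0.25; α err prob = 0.05; and power (1 − β err prob) = 0.80" for a within-between interaction. The number of groups, number of measurements and correlation are not stated, so 11 cannot be confirmed. With two groups and correlation 0.5 the formula gives 21 (five measurements) or 24 (four). It gives 11 with correlation 0.75 and five measurements, or 0.80 and four. That calculation concerns a different test and does not bear on this point.

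**Inputs.** n = 20 (section 2.2.2); k = 5 (section 2.4) or k = 4 (section 2.3.2); alpha 0.05 (section 2.4). Assumed: two-sided tests, no ties, Bonferroni over all m = k(k−1)/2 pairs.

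**Formulas.** SE of a mean-rank difference = √(k(k+1)/(6n)); z = gap/SE; adjusted p = m × two-sided p; critical gap = z(1 − 0.05/(2m)) × SE.

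| | k = 5 | k = 4 |
|---|---|---|
| SE | √(30/120) = 0.500 | √(20/120) = 0.408 |
| Pairs m | 10 | 6 |
| Critical gap | 2.807 × 0.500 = 1.40 | 2.638 × 0.408 = 1.08 |
| Gap 1: z, raw p | 2.00, 0.0455 | 2.45, 0.0143 |
| Gap 1: adjusted p | 0.46 | 0.086 |
| Gap 2: adjusted p | 0.0006 | 0.000006 |
| Gap 3: adjusted p | 0.00000002 | below 0.000001 |

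**Strictly stepwise recovery.** Suppose that in all 20 participants the order from worst to best is post-fatigue, immediate, 15 min, (30 min), baseline. Post-fatigue against immediate has gap exactly 1 and is not significant with either k. Post-fatigue against 15 min has gap 2, and against 30 min gap 3; both are significant. A gap of 1 would need n = 40 (k = 5) or n = 24 (k = 4). An exact sign test on 20 of 20 improvements gives 2 × 0.5^20 = 0.0000019, or 0.000019 after a tenfold correction.

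**Other patterns with all 20 improving (k = 5, simulated).** The mean gap is about 2.5 for full recovery to a plateau, 2.0 to 2.2 for partial recovery to a plateau, and 2.6 to 3.0 for immediate recovery that wanes. Dunn was significant in at least 99.9% of runs in each. In a stepwise pattern with noise equal to the step, the mean gap is 1.36 and 32% of runs were significant.

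**Power without requiring that all improve.** The means and SDs here are assumptions, since the plan gives none. The outcome is log-normal, n = 20, 1,500 runs, k = 5, all-pairs Bonferroni for both tests. Log means are in the order baseline, post-fatigue, immediate, 15 min, 30 min. The contrast is post-fatigue against immediate.

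| Pattern | Within-person SD | Dunn | Wilcoxon signed-rank |
|---|---|---|---|
| Stepwise (0, −0.5, −0.3, −0.2, −0.1) | 0.10 | about 9% | 99% |
| Stepwise | 0.15 | about 14% | about 80% |
| Stepwise | 0.20 | about 13% | about 45% |
| Partial plateau (0, −0.5, −0.3, −0.3, −0.3) | 0.15 | about 45% | about 78% |
| Partial plateau | 0.20 | about 25% | about 46% |

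With four assessments, the stepwise pattern at SD 0.15 gives about 33% against 83%. In the five-assessment stepwise pattern, less noise does not rescue Dunn: at SD 0.05 its power is 0% and Wilcoxon's 100%. Under full or waning recovery Dunn reaches 98 to 100% for the immediate contrast. For post-fatigue against 15 min in the stepwise pattern at SD 0.15, Dunn has about 91% (five assessments) or 97% (four).

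**The case against.** Friedman followed by Dunn is a recognised procedure with controlled type I error. Lower power in one branch is a weakness of choice and not an error or contradiction. That stands, and it is why this is a suggested improvement.

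Three stronger readings are tempting, and the documents support none of them.

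- A reader might infer that the contrast fails whenever all 20 improve. Universal improvement guarantees only a gap of at least 1; the gap can reach 4 with five assessments. Nothing in the article says recovery will be strictly stepwise. Passive recovery lasts 24 minutes before its immediate assessment (section 2.3.4.2), so a plateau is at least as plausible.
- A reader might infer that stepwise recovery cannot be detected at all. Even in the strict ladder the 15- and 30-minute contrasts are clearly significant. Only the adjacent step is lost.
- A reader might infer that the main hypothesis is compromised. The abstract's hypothesis is active against passive recovery, which section 2.4 gives to Kruskal-Wallis or the repeated-measures ANOVA.

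The all-pairs family is also an assumption. Without adjustment a gap of 1 gives p = 0.046 with five assessments. With only two planned contrasts and four assessments it gives 2 × 0.0143 = 0.029. Part of the loss therefore comes from the size of the family. Finally, the article does not show which variables, if any, will fail Shapiro-Wilk.

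What remains is that the recovery shape is unknown in advance, and the named test does poorly under some plausible shapes where a paired test does not.

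**Conclusion.** The point holds in limited form. For non-normal variables, at n = 20, two assessments that hold adjacent ranks in every participant cannot be separated by Dunn's test after all-pairs Bonferroni: adjusted p is 0.46 with five assessments and 0.086 with four. In a strictly stepwise recovery this makes the immediate step non-significant even if all 20 improve. Under noisy partial recovery the step is not impossible to detect, but power is well below that of a paired test at the same correction. Under full or waning recovery there is little loss for the immediate contrast.

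The p values rest on two-sided tests, no ties and an all-pairs family. The power figures rest on assumed means and SDs and are illustrative. The scope is within-modality tests of variables that fail Shapiro-Wilk. This is a cheap gain in power and not a flaw that invalidates the plan.

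**What to change.** In section 2.4, replace Dunn's post hoc test with Wilcoxon signed-rank tests on planned within-modality contrasts: post-fatigue against each post-recovery assessment actually made. These are the immediate and 15-minute assessments, and the 30-minute one if it is kept once sections 2.3.2 and 2.4 are reconciled. The change should not settle that discrepancy silently. Adjust the contrasts by Holm within each variable and modality, and report the Hodges-Lehmann shift with its confidence interval. Keep Friedman as the omnibus test.

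The cost is about one sentence of analysis text, with no new data or participants. There are two downsides. Pairs outside the planned contrasts are no longer formally tested. The signed-rank test also assumes roughly symmetric paired differences; where that is doubtful, use a sign test or analyse on a log scale, and say so in advance.

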## Abstract

Prolonged periods of sitting at work can increase trunk muscle fatigue from the continuous contraction of deep trunk muscles. Insufficient activity of these muscles can decrease muscular support to the spine and increases stress on its passive structures. This can lead to reduced spinal mobility and impaired postural stability. It may also stimulate nociceptor activity leading to pain. However, frequently used recovery modalities such as muscle strengthening and stretching exercises, can be time-consuming, impractical, and difficult to implement in the workplace. Diaphragmatic breathing exercises, which increase the activity of the deep trunk muscles by raising intra-abdominal pressure, seem to be a suitable alternative. However, little is known as to what extent diaphragmatic breathing exercises contribute to the reduction of fatigue induced by prolonged sitting. This paper presents a study protocol that aims to investigate the acute effect of diaphragmatic breathing exercises on recovery of fatigue-induced changes in spinal mobility and postural stability in sedentary middle-aged adults at risk of developing non-specific low back pain. Twenty sedentary adults aged between 25 and 44 years will perform Abt’s fatigue protocol, followed by 1) active recovery using diaphragmatic breathing exercises and 2) passive recovery in the form of lying on the bed, respectively. There will be 1 week of rest in-between. Pre-fatigue, post-fatigue, and after the active and passive recovery, spinal mobility and postural stability will be evaluated using the spinal mouse device and a posturography system, respectively. The electromyography will be used to determine the muscle-fatigue conditions. We hypothesize that active recovery in a form of diaphragmatic breathing exercises would be more effective in restoring spinal mobility and postural stability followed by the fatigue of back and hamstring muscles compared to passive recovery in sedentary adults. Increasing core and respiratory muscle strength via these exercises could be beneficial for overall mobility and stability of the spine. Reducing compressive stress on the passive structures of the spine may be also beneficial for lowering low back pain. Therefore, we believe that diaphragmatic breathing exercises have the possibility to be incorporated into the workplace and contribute to better back health in sedentary middle-aged adults.

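### Each participant appears to receive both recovery modalities, but section 2.4 compares them as independent groups, which makes the per-assessment comparisons and the modality main effect too conservative

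*Protocol article*

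**What the plan says.** **Design.** The Abstract has twenty adults perform the fatigue protocol, "followed by 1) active recovery using diaphragmatic breathing exercises and 2) passive recovery in the form of lying on the bed, respectively". It adds: "There will be 1 week of rest in-between". Section 2.3.2 collects data from all participants, including after both the active and the passive modality. No section shown allocates people to two groups.

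**Analysis.** Section 2.4 introduces two experimental groups, A and B, which appear nowhere else in the text. For non-normal data it uses Friedman's test across assessment times, and a Kruskal-Wallis "test will be used for the inter-group comparisons (experimental group A vs. experimental group B) at each assessment". For normal data it uses a repeated-measures ANOVA with assessment time as the five-level repeated factor, "and the two groups (experimental group A vs. experimental group B) as independent factors". It calls this ANOVA five-way, although it names two factors.

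**Sample size.** Section 2.2.2 gives "statistical test = repeated measures, within - between interaction", "effect size F = 0.25", "α err prob = 0.05" and power 0.80. The result is 11 subjects, raised to about 20 to allow for dropouts.

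**The concern.** A week of rest between two modalities makes sense only if the same person does both. The active and passive measurements at any assessment are then pairs. Kruskal-Wallis with two groups is a rank-sum test for independent samples and ignores the pairing. An ANOVA with group as a between-subject factor does the same for the modality main effect. Section 2.4 recognises repeated measurement across time, through Friedman's test, but drops it across modality.

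The stated hypothesis is that active recovery restores spinal mobility and postural stability better than passive recovery, so the mismatch falls on the study's central comparison. When pairs are analysed as independent samples, stable differences between people stay in the error term. With about 20 people, a null result could then come from the choice of test and not from the absence of an effect.

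**Working it through.** **1. The plan's own figure.** For a within-between interaction with k groups, m measurements and sphericity, lambda = f²·N·m/(1-r), with df1 = (k-1)(m-1) and df2 = (N-k)(m-1). Here r is the correlation between time points. Section 2.2.2 does not report k, m or r, so 11 cannot be confirmed. Section 2.4 lists five assessments and section 2.3.2 lists four, so both values of m were tried, with k = 2 and f = 0.25:

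- m = 5, r = 0.5, N = 11: lambda = 0.0625 × 11 × 5/0.5 = 6.875, df 4 and 36, power 47%. N = 21 is needed for 80%, or 22 for equal groups.
- m = 4, r = 0.5: N = 24 is needed.
- N = 11 results if r is about 0.75 to 0.77 (m = 5) or 0.79 to 0.80 (m = 4). For example, with m = 5 and r = 0.75, lambda = 13.75 and power is 80%.

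So 11 is attainable under a high, unstated correlation. Whatever r was used, the chosen test treats group as a between-subject factor.

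**2. Standard error at one assessment.** Inputs: n = 20 (Abstract), alpha 0.05 (sections 2.2.2 and 2.4). Assumptions not in the documents: outcome SD 1 in each session, modality difference 0.5 SD, two-sided test, and between-session correlation rho from 0.3 to 0.8.

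- Paired SE = sqrt(2(1-rho)/20)
- Unpaired SE = sqrt(2/20) = 0.316
- Ratio = 1/sqrt(1-rho)

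At rho = 0.5 the paired SE is 0.224 and the ratio 0.316/0.224 = 1.41. Paired power comes from the noncentral t with 19 df and noncentrality 0.5/SE, which is 0.5/0.224 = 2.24 at rho = 0.5. Unpaired power and type I error come from simulating the same correlated pairs and applying the two-sample t-test.

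| rho | SE ratio | Paired power | Unpaired power | Relative loss | Unpaired type I error (nominal 5%) |
|---|---|---|---|---|---|
| 0.3 | 1.20 | 43% | 31% | 28% | 2% |
| 0.5 | 1.41 | 56% | 29% | 49% | 0.7% |
| 0.7 | 1.83 | 78% | 25% | 69% | 0.1% |
| 0.8 | 2.24 | 92% | 22% | 76% | below 0.1% |

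The rank tests behave alike. Wilcoxon signed-rank against Kruskal-Wallis gives 41% against 29%, 55% against 28%, 76% against 24%, and 91% against 21%. Kruskal-Wallis type I error is 2.1%, 1.0%, 0.2% and 0.03%.

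**3. The ANOVA.** This was simulated with 20 people, two sessions and four assessments. Assumed variances: person 0.5, person-by-session 0.1, person-by-time 0, 0.1 or 0.2, and a residual that brings the total to 1. Under the alternative, the modalities differ by 0.4 SD at the last two assessments. Each cell gives group treated as between-subject, then modality treated as within-person.

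| Person-by-time variance | Interaction type I error | Interaction power | Main-effect type I error | Main-effect power |
|---|---|---|---|---|
| 0 | 4.9% / 5.0% | 35% / 34% | 0.1% / 4.6% | 2% / 27% |
| 0.1 | 1.6% / 5.0% | 29% / 44% | below 0.1% / 5.1% | 1% / 30% |
| 0.2 | 0.2% / 5.0% | 20% / 63% | below 0.1% / 5.2% | 1% / 34% |

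The interaction is unharmed when the between-session correlation comes only from a stable personal level, because that level is removed within each session. It turns conservative when people repeat the same time profile in both sessions. The main effect is badly conservative in every case.

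**The case against.** **The wording about factors is ambiguous.** In section 2.4, "the two groups (experimental group A vs. experimental group B) as independent factors" stands opposite the outcome as dependent factor, so it may only mean independent variables. This stands for that phrase alone. Kruskal-Wallis and the within-between test in section 2.2.2 both point to independent groups, and no paired between-modality test is named anywhere. Calling the model five-way is probably a slip for five levels and changes no error term.

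**Separate groups may be intended.** Sections 2.2.2 and 2.4 suggest groups, the Abstract and section 2.3.2 suggest one cohort, and Figure 1 is not shown. A reader might infer that the groups certainly do not exist. The text favours one cohort but does not settle the matter.

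**Kruskal-Wallis is conditional.** It applies only to data that fail the normality test, and the parametric route names no unpaired test at each assessment. This is true, but the parametric route still carries the misplaced group factor.

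**The interaction may be sound.** A reader might infer that every between-modality standard error is wrong. Step 3 of the working shows otherwise, and the interaction is the effect on which section 2.2.2 sizes the study. This objection stands in full for that effect when people have no repeatable time profile.

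**Counting 20 people as 40 sounds anti-conservative.** With positive correlation it is not. The extra degrees of freedom (38 against 19) are far outweighed by the inflated standard error.

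**Conclusion.** The design as described and the analysis as stated contradict each other and must be reconciled before data are analysed. If modality is within-person, the per-assessment comparisons and the modality main effect have standard errors too large by 1/sqrt(1-rho), that is 1.20 to 2.24 for rho from 0.3 to 0.8. Tests run well below their nominal 5% and real differences are more likely to be missed.

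The power figures rest on an assumed 0.5 SD difference and an assumed range of rho, neither of which the documents give. A reader might infer that most of the power is lost. That holds only above rho of about 0.5, and at 0.3 the relative loss is 28%. Nor can the correlation implied by N = 11 be borrowed to settle this, because it relates time points and not sessions.

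**What to change.** - In section 2.4, replace group A against group B with modality as a within-participant factor. Use a two-way repeated-measures ANOVA (modality and time both within participant), or a mixed model with random effects for participant and for session within participant.
- At each assessment, use a paired t-test or a Wilcoxon signed-rank test in place of Kruskal-Wallis.
- Call the ANOVA two-way instead of five-way.
- In section 2.2.2, restate the calculation for the within-participant test and report the number of measurements and the assumed correlation.
- Add a period effect only if the order of modalities varies between participants. The Abstract reads as one order, active then passive, and in a single fixed order modality and period cannot be separated.
- If two separate groups are really intended, leave the between-group tests and correct the Abstract and section 2.3.2 instead.

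**Cost.** For the analysis, wording and standard procedures, with no extra data. The sample-size calculation has to be rerun and may not return 11. Varying the order of modalities so that a period effect can be fitted would be a change of design, not of wording.
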